# The FIB-PPH trial: fibrinogen concentrate as initial treatment for postpartum haemorrhage: study protocol for a randomised controlled trial

**DOI:** 10.1186/1745-6215-13-110

**Published:** 2012-07-17

**Keywords:** Postpartum haemorrhage, Haemostasis, Blood transfusion, Fibrinogen concentrate, Obstetrics, Thrombelastography, Coagulation

## Abstract

**Background:**

Postpartum haemorrhage (PPH) remains a leading cause of maternal mortality worldwide. In Denmark 2% of parturients receive blood transfusion. During the course of bleeding fibrinogen (coagulation factor I) may be depleted and fall to critically low levels, impairing haemostasis and thus worsening the ongoing bleeding. A plasma level of fibrinogen below 2 g/L in the early phase of postpartum haemorrhage is associated with subsequent development of severe haemorrhage. Use of fibrinogen concentrate allows high-dose substitution without the need for blood type crossmatch. So far no publications of randomised controlled trials involving acutely bleeding patients in the obstetrical setting have been published. This trial aims to investigate if early treatment with fibrinogen concentrate reduces the need for blood transfusion in women suffering severe PPH.

**Methods/Design:**

In this randomised placebo-controlled double-blind multicentre trial, parturients with primary PPH are eligible following vaginal delivery in case of: manual removal of placenta (blood loss ≥ 500 ml) or manual exploration of the uterus after the birth of placenta (blood loss ≥ 1000 ml). Caesarean sections are also eligible in case of perioperative blood loss ≥ 1000 ml. The exclusion criteria are known inherited haemostatic deficiencies, prepartum treatment with antithrombotics, pre-pregnancy weight <45 kg or refusal to receive blood transfusion. Following informed consent, patients are randomly allocated to either early treatment with 2 g fibrinogen concentrate or 100 ml isotonic saline (placebo). Haemostatic monitoring with standard laboratory coagulation tests and thromboelastography (TEG, functional fibrinogen and Rapid TEG) is performed during the initial 24 hours.

Primary outcome is the need for blood transfusion. To investigate a 33% reduction in the need for blood transfusion, a total of 245 patients will be included. Four university-affiliated public tertiary care hospitals will include patients during a two-year period. Adverse events including thrombosis are assessed in accordance with International Conference on Harmonisation (ICH) good clinical practice (GCP).

**Discussion:**

A widespread belief in the benefits of early fibrinogen substitution in cases of PPH has led to increased off-label use. The FIB-PPH trial is investigator-initiated and aims to provide an evidence-based platform for the recommendations of the early use of fibrinogen concentrate in PPH.

**Trial registration:**

ClincialTrials.gov NCT01359878.

## Background

Optimal haemostatic capacity during excessive bleeding reduces mortality, blood loss and the need for transfusions [1]. Pregnancy induces changes in coagulation towards a more procoagulant state with mild thrombocytopenia, increased procoagulant factors and diminished fibrinolysis [2], ultimately serving as physiological protection against postpartum bleeding. However, postpartum haemorrhage (PPH) remains a leading cause of maternal mortality and morbidity worldwide [3]. In Europe, 1.75 % of births are complicated by severe PPH (blood loss > 1000 ml) [4] with the risk of death in western countries at 1:100,000 births [5].

### Hypofibrinogenaemia during postpartum haemorrhage

Acquired hypofibrinogenaemia develops early in relation to fluid resuscitation, imbalanced transfusion of blood components and bleeding [6]. This state of impaired haemostasis also develops in relation to PPH [7-9]: a study of 128 women suffering from PPH (blood loss of approximately 1000 ml) investigated by Charbit *et al*. [7] evaluated the impact of coagulation on the course of bleeding. The fibrinogen plasma level was identified as the only early independent predictor of the subsequent development of severe PPH. A fibrinogen level of below 2 g/L implied a positive predictive value of 100% for the development of severe PPH, whereas a level of below 4 g/L implied a negative predictive value of 76%. ‘Severe PPH’ was defined as: ‘decrease of haemoglobin (Hb) > 4 g/dL (>2.5 mmol/L), transfusion of at least four red blood cell (RBC) units, haemostatic intervention (angiographic embolisation, surgical arterial ligation or hysterectomy) or death’.

### Fibrinogen concentrate

Fibrinogen is essential in the development of a strong and functional blood clot. It is produced in the liver and the average plasma level is 2.0 to 4.5 g/L [10]. In relation to pregnancy (especially the third trimester) the level of fibrinogen rises to an average of 5 g/L [11]. Several studies addressing different clinical contexts of bleeding associate a low level of fibrinogen with increased transfusion of blood products and amount of blood loss during operation [8,10,12-18]. No optimal plasma level of fibrinogen has so far been established [10,19-21]. Fibrinogen concentrate is a commercially available drug produced from human plasma [22]. It undergoes viral inactivation and does not require blood match or thawing prior to use. Traditionally, acquired hypofibrinogenaemia is treated with fresh frozen plasma (FFP) or cryoprecipitate (Cryo) containing 2.5 g [10,19] and 15 g per litre [16] respectively. Both blood products require thawing and crossmatch before infusion. Thus, with FFP a volume of 800 ml would be required to substitute 2 g of fibrinogen, corresponding to 133 ml of Cryo. However, the use of FFP is associated with several transfusion-related complications [23] rendering it a suboptimal treatment for early prevention of fibrinogen deficiency. Cryo is a pooled plasma product with one unit of Cryo exposing the recipient to approximately four to six donors [24].

Only four randomised controlled trials (RCT) investigating fibrinogen concentrate have been published so far. One trial investigated the potential of fibrinogen concentrate to reverse a colloid-induced impairment of haemostasis (that is, coagulopathy) in elective surgical patients undergoing radical cystectomy (n = 20) [25]. Two trials explored elective cardiac surgery (n = 20 [26], n = 31 [27]). One trial included severely bleeding elective surgical patients (n = 43) and investigated partial replacement of FFP with fibrinogen concentrate [28]. None of these studies were designed to evaluate a clinical outcome, but indicated improved haemostasis [25,28] and a potential ability to reduce the rate of blood transfusion [25,27]. To our knowledge, no RCT has been published addressing the effect of fibrinogen in acutely bleeding patients or obstetric conditions. However, several publications have described experience from clinical use of fibrinogen concentrate [8,18,29-34] including a total of 144 cases of severe PPH with massive transfusion. In these cases, treatment with fibrinogen concentrate seems to be rapid and efficient in treating hypofibrinogenaemia without any serious adverse events reported in the obstetrical subpopulation. An incidence of 3.48 thrombotic events per 10^5^ treatments, using 4 g of fibrinogen concentrate in different clinical settings was reported in a recent pharmacosurveillance for the period of 1986 to 2008 in 21 countries [35].

### Need for a trial

The FIB-PPH trial will potentially provide evidence-based knowledge on the feasibility of an early use of fibrinogen concentrate in PPH. Though the trial is not powered to show a potential lifesaving effect, an effective treatment reducing the need of red blood cell transfusion could be beneficial. Allogenic blood transfusions are associated with increased mortality and morbidity [36,37]. Besides the potential risk of disease transmission, an immune modulation caused by the transfusion of allogenic blood seems to increase the incidence of infections, cancer relapse, transfusion-related lung injury [19,21] and non-infectious serious hazards of transfusion [23] and is associated with the phenomena of microchimerism [38,39]. Means to reduce allogenic blood transfusions are currently being widely searched for and examined.

Fibrinogen concentrate is increasingly being used in the treatment of PPH. However, this remains off-label use and is based on a low level of evidence. It is of utmost importance to establish sound evidence before a general implementation in the clinical setting. We need to perform high-level RCTs before a more widespread use of fibrinogen concentrate can be recommended.

Following the previously described work by Charbit *et al*. [7] a high-quality trial addressing this matter is needed in order to secure evidence-based treatment and optimal use of economic resources.

### Objective

The aim of this study is to evaluate whether initial treatment with fibrinogen concentrate reduces the need for allogenic blood transfusion in postpartum haemorrhage (PPH). Other potential benefits and harms will be assessed as secondary outcomes.

## Methods and design

### Overview

We are conducting a multicentre parallel placebo-controlled randomised double-blind clinical trial with 1:1 allocation ratio. The trial is investigator initiated and controlled and good clinical practice (GCP) monitored.

### Inclusion criteria

Inclusion is possible if the following eligibility criteria are met: 1) Informed consent from participant. 2) Age ≥ 18 years. 3) PPH defined as bleeding from uterus and/or the birth canal within 24 hours postpartum. 4) Vaginal delivery and in need of anaesthesiological assistance and either: a) estimated blood loss exceeding 500 ml and intended manual removal of placenta; or b) estimated blood loss exceeding 1000 ml and intended manual exploration of the uterus due to continuous bleeding after the birth of placenta. 5) In case of birth by caesarean section and estimated perioperative blood loss exceeding 1000 ml (Figure 1).

**Figure 1 F1:**
[figure not shown]
**Trial flow.** Patients scheduled for caesarean section or developing postpartum haemorrhage following vaginal delivery will be screened for inclusion/exclusion and asked for consent to participate. Baseline blood samples are taken before intervention and patients are randomised to either intervention (fibrinogen concentrate) or placebo (saline). Haemostatic monitoring (blood samples) is performed 15 minutes, 4 hours and 24 hours post-intervention together with a clinical status.

### Exclusion criteria

Participants fulfilling one or more of the following criteria will be excluded: 1) Known inherited deficiencies of coagulation. 2) Anti-thrombotic treatment prepartum due to increased risk of thrombosis. 3) Pre-pregnancy weight <45 kg. 4) Refusal to receive blood transfusion.

### Randomisation and blinding

Allocation sequence is produced by a third party (pharmacologists at Glostrup Pharmacy, Glostrup, Denmark) using computer generation fixed block size with stratification by centre. Allocation concealment is secured by using sealed opaque numbered envelopes specially prepared for this trial and this unique number is used as patient trial ID. Participants, outcome assessors, trials investigators, statisticians and GCP trial monitors are blinded, as well as care providers such as midwives, obstetricians, anaesthesiologists and anaesthetist nurses. Anaesthetic personnel not involved in patient care randomise the patient and dispense the trial medicine. Two 50 ml opaque syringes (yellow coloured) will be delivered to the operating theatre without revealing the allocation. We register the success of blinding by asking the responsible team/physician in the operating theatre following administration if he or she has any hint of the allocated treatment and if yes, why. The patient is asked during the follow-up period.

### Intervention

The participants are assigned to either 1) placebo (100 ml isotonic saline) i.v. or 2) the intervention drug: 2 g of fibrinogen concentrate (Haemocomplettan/Riastap, CSL Behring, Marburg, Germany) i.v. given via an infusion pump in 20 minutes. We use a fixed dose for all patients randomised to the intervention group without prior clinical assessment of the fibrinogen level. This strategy is primarily based on the clinical urgency since the treatment is required to be administered as early as possible following the inclusion. Dosage is based on a target level of 4 g/L [7] and a mean fibrinogen level in women with 500 to 1000 ml blood loss of 3.4 g/L [9]. Thus, we calculated the optimal dose using two different methods [10,25] in order to increase the level approximately 0.6 g/L in the average 65.9 kg fertile woman in the Danish capital area (based on data from the Danish National Board of Health) taking either the increased plasma volume or weight gain during pregnancy into account. An optimal dose of 2.2 to 2.7 g was identified. However, considering the prothrombotic state of pregnancy and postpartum period and the fact that previous controlled clinical studies investigated patients that were highly diluted with colloids [25] or affected by the coagulopathies of extracorporeal circulation [26,27], we pragmatically chose 2 g of fibrinogen concentrate as the intervention dose.

### Setting, location and follow-up

Parturients will be included during a two-year period at the four largest hospitals in the Capital Region, Denmark. These four centres are university-affiliated public tertiary care hospitals in the Copenhagen area each with 3500 to 7000 deliveries per year. Parturients are invited to participate at the pre-anaesthetic evaluation and will be hospitalised for at least 24 hours following inclusion. Participants are contacted by phone six weeks after the intervention, and they are able to contact the principal investigator during the full trial period. Blood transfusion and the use of tranexamic acid and other haemostatic agents follow Danish standard recommendations in all four centres and adherence to guidelines will be monitored as part of the conduction of this trial.

### Outcomes and safety measures

The primary outcome is the need for transfusion with allogenic blood products. Secondary outcomes will be development of ‘severe PPH’ defined as: ‘decrease of haemoglobin (Hb) of > 4 g/dl (2.5 mmol/L), transfusion of at least four red blood cell (RBC) units, haemostatic intervention (angiographic embolization, surgical arterial ligation or hysterectomy) or death. We also evaluate estimated blood loss, total amount of blood transfused, the development of re-bleeding and Hb < 5.8 g/dL (3.6 mmol/L)’. We will register potential side effects such as: fever, headache, nausea, vomiting, allergic reactions, anaphylaxis and thromboembolic complications (deep venous thrombosis, acute myocardial infarction and pulmonary embolism) [40]. All suspected unexpected serious adverse reactions will also be reported in accordance with the International Conference on Harmonisation (ICH) GCP and the Danish Medicines Agency guidelines.

### Monitoring and data collection

Adherence to ICH GCP, including the Helsinki Declaration, and trial protocol is being monitored by independent monitors from the GCP unit at Copenhagen University, and data are being collected on paper case report forms. Transfusion data are assessed through multiple data sources including the Capital Region Blood Banks blood product registration system in which all used blood products are registered together with the recipient patients’ unique personal identification (cpr) number. This ensures an almost complete follow-up excluding only patients withdrawing consent to participate.

### Haemostatic monitoring

Blood samples are drawn at inclusion before intervention and at 15 minutes, 4 hours and 24 hours following the termination of infusion. Blood transfusions, fluid therapy, use of uterotonic and haemostatic drugs, and amount of blood loss are assessed by anaesthetic personnel before administration, 4 hours and 24 hours after. We use haemostatic tests thrombelastography (TEG, functional fibrinogen and Rapid TEG by Haemoscope Inc., Niles IL, USA) as well as standard tests such as haemoglobin, factor level 2,7,10 (including international normalised ratio (INR)), activated partial thromboplastin time (APTT), D-dimer, antithrombin III and platelet count. Plasma fibrinogen level is measured at all four time points but only the post-interventional measurements will be available for clinical evaluation and treatment aspects. Samples are collected and frozen for later analysis.

### Number of participants

Approximately 1% of parturients receive blood transfusion [7,9,32,41-44] and 1.75% develop PPH (blood loss >1000 ml) [4]. No studies conducted in the obstetric target population were available during the design phase of this trial, however, the two available RCTs found a respectively 60% [25] and 20% but insignificant [26] risk reduction in the need for allogenic blood transfusions. Thus, we settled to investigate a risk reduction of 33%: with α = 0.05 and power (β) = 80%, a number of 107 patients in each group are needed in order to evaluate a 33% reduction in the need for blood transfusion. With a margin for missing data and dropouts of 15% - a total of 245 patients will be included.

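### Read as a loss rate, the 15% margin is not quite covered by 245 women: 208 would remain against 214 required (minor arithmetic slip)

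*Protocol article*

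**What the plan says.** All the figures stand in the section Number of participants of the protocol article. The design values are "with α = 0.05 and power (β) = 80" per cent, with a target described as "Thus, we settled to investigate a risk reduction of 33" per cent. From these the article concludes that "a number of 107 patients in each group are needed in order to evaluate a 33% reduction in the need for blood transfusion". It then moves from the required number to the planned number: "With a margin for missing data and dropouts of 15% - a total of 245 patients will be included". The abstract repeats the total ("a total of 245 patients will be included"), and the Discussion uses the same figure.

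Two other places bear on the point. The Overview describes a "randomised double-blind clinical trial with 1:1 allocation ratio". The section Monitoring and data collection, describing transfusion records drawn from several sources including the regional blood bank system, says: "This ensures an almost complete follow-up excluding only patients withdrawing consent to participate".

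**The concern.** A margin for missing data and dropouts exists so that the required number is still there after the losses. Such losses occur among women who have been included, so the natural test is whether 214 remain when 15% of 245 are gone. They do not. The pattern suggests a common slip: adding 15% to the required number instead of dividing it by 0.85.

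What is at stake is whether the sample-size statement is accurate. A reader is told that the trial keeps its planned 80% power with up to 15% loss, when the true limit is a little lower.

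**Working it through.** **Inputs, all from Number of participants:** 107 required per group; margin 15%; planned total 245. Equal allocation comes from the Overview.

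**Required evaluable women:** 2 × 107 = 214.

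**Reproducing 245**
- As an add-on: 214 × 1.15 = 246.1. The planned 245 is about one woman below this; 245/214 − 1 = 14.5%.
- As a loss rate: 214/(1 − 0.15) = 251.8, so 252 (126 per group). The planned 245 is 7 below this.

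The add-on form comes much closer, so it is the likely origin, with some rounding. Neither form gives exactly 245.

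**What 245 delivers**
- After a 15% loss: 245 × 0.85 = 208.25, so 208 women or 104 per group. Shortfall: 214 − 208 = 6 women, or 6/214 = 2.8%.
- Largest loss that still leaves 214: 245 − 214 = 31 women, and 31/245 = 12.65%.

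**Effect on power.** The article gives no control-group transfusion rate, so one must be assumed. Taking 33% as a relative reduction, I solved for rates at which 107 per group gives 80% power. The formula, two-sided and without continuity correction, is

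power = Φ{ [ |p1 − p2| √n − 1.96 √(2 p̄(1 − p̄)) ] / √( p1(1 − p1) + p2(1 − p2) ) }

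with p1 = 0.578, p2 = 0.67 × 0.578 = 0.387 and p̄ = 0.483.
- n = 107: (1.973 − 1.385)/0.694 = 0.848, power 80.2%.
- n = 104: (1.945 − 1.385)/0.694 = 0.807, power 79.0%.
- n = 122.5 (all 245 evaluable): (2.111 − 1.385)/0.694 = 1.047, power 85.2%.

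The drop hardly depends on the assumption:

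| Assumed rates | Test | Power at 107 per group | Power at 104 per group |
|---|---|---|---|
| 57.8% v 38.7% | two-sided, uncorrected | 80.2% | 79.0% |
| 60% v 40% | two-sided, continuity-corrected | 80.1% | 78.9% |
| 50.2% v 33.5% | one-sided, uncorrected | 80.2% | 79.2% |

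In each case the cost of a full 15% loss is about 1 percentage point.

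**The case against.** The strongest reply is that the article speaks of a margin and does not say that 15% of included women are expected to be lost. If the margin is simply 15% added to 214, the answer is 246.1, and 245 is within about one woman of it. This largely stands: the wording is ambiguous and an add-on is a common convention. It does not fully rescue the sentence, because 245 is still slightly short on that reading, and because a margin for missing data and dropouts is most naturally a share of the women included.

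A second reply is that a 15% loss is unlikely. The blood bank system should make the primary outcome nearly complete. The section Statistical methods and data analysis also provides worst-case and best-case analyses, then multiple imputation if needed, once missing data exceed 5%, so women with missing data need not drop out of the analysis. This stands too, with one qualification: the same section removes from the intention-to-treat set women found ineligible after randomisation and those without standing consent, so they also use up the allowance of 31.

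A reader might infer two stronger things. One is that an odd total conflicts with equal allocation. It does not: the article fixes an allocation ratio, not equal final counts, and randomisation is in blocks within four centres, so arms of 123 and 122 are compatible with it. The other is that the trial is underpowered and should enrol more women. The figures do not support this: the gap is 6 evaluable women, it opens fully only if 15% are lost, and the article expects much less loss on the primary outcome.

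**Conclusion.** A minor arithmetic error. With 15% read as a loss rate, 245 leaves 208 evaluable women where 214 are required; the loss it can absorb is 12.65%. With 15% read as an add-on, 245 is short by about one woman. The cost is about 1 percentage point of power if 15% are truly lost, and nothing if loss stays at or below 12.65%.

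The counts follow from the article's own figures. The power values rest on control rates chosen to reproduce 107 per group, because the article states none; they show the size of the effect and are not the trial's design values. The slip does not undermine the design or the planned analysis.

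**What to change.** Change one sentence in Number of participants, in either of two ways:
- Keep the total and correct the margin: '245 patients allow for about 12.6% missing data and dropouts'. The exact limit is 31 of 245, 12.65%; rounding down avoids overstating it.
- Keep 15% as the loss rate and state what would remain: about 104 per group and about 79% power, with the assumed control rate given alongside.

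Either way, the sentence should make clear that the percentage is a share of the women included. No extra enrolment is needed, and because the total stays at 245, the abstract and Discussion need no change. The cost is the rewording of that sentence.

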### Statistical methods and data analysis

The two groups will be compared using chi-square test (binominal data) or Fischer’s exact test if numbers of expected values are less than five (or an unconditional exact test). Fibrinogen concentrate can potentially reverse the impaired haemostasis observed when using colloids [25,45]. The potential effect of fibrinogen concentrate may rely on the pre-administered use of colloids, so sensitivity analysis and the influence of this will be assessed together with other possible confounders (baseline variables/parameters are presented in Table 1). In accordance with ICH GCP recommendations on statistical principles for clinical trials (E9) [46], we will present adjusted and unadjusted analyses of the possible effect. The baseline variables/parameters will be assessed using multiple logistic regression models. The evaluation of pre-specified subgroups demands more participants than planned in this trial, however, to explore and guide further trials in this area we will perform two subgroups analysis: one on mode of delivery (vaginal versus caesarean section) and one on parturients with hypofibrinogenaemia at intervention, thus guiding upcoming trials in their selection of study population. All outcomes will be reported as ‘intention-to-treat’ analysis including all randomised patients fulfilling inclusion criteria and not meeting exclusion criteria with a standing consent to participate. Patients with the following major protocol violations will not be included in a supplemental per-protocol analysis: not receiving total dose and lack of follow-up. The impact of blinding level will be explored in a separate sensitivity analysis. Statistics will be performed before the code of allocation is revealed. If the overall level of missing data is less than 5%, we will perform complete case analysis. If more than 5% of missing data is the case, we will present ‘worst-case’ and ‘best-case’ analyses and if those are inconclusive, we will perform multiple imputations [47].

**Table 1 T1:** List of baseline parameters/variables to be assessed for baseline imbalance between treatment groups in the final analysis

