**Baseline parameter/variable**	
The level of fibrinogen before intervention defined by Clauss method (g/L)	
Presence of hypofibrinogenaemia before intervention defined by Clauss method (<2 g/L) and equivalent functional fibrinogen (TEG) MA (< 14 mm or according to validation in this study).	
Hypocoagulability prior to intervention measured with standard TEG: R-time >8 min or alpha angle <55° or MA <50 mm or LY30 >8 %	
Crystalloids used prior to intervention (ml)	
Colloids used prior to intervention (ml)	
The use of tranexamic acid prior to intervention (yes/no)	
Mode of delivery	Caesarean section
	Vaginal delivery
Post vaginal procedure	Intended manual removal of placenta
	Manual exploration of the uterus due to continuous bleeding after the birth of placenta
Estimated blood loss before intervention (ml)*	
Primary cause of PPH:	
**TRAUMA of the birth canal:** paravaginal haematoma, cervical laceration, vaginal laceration, perineal laceration, uterine rupture	
**Retained TISSUE:** Retained placental tissue, Percrete or accrete placenta	
**Impaired THROMBOSIS:** disseminated intravascular coagulation, placental abruption, severe pre-eclampsia	
**Reduced TONE of uterus:** uterine atony	
Weight of parturient (kg) (because dose of fibrinogen = 2 g/BW kg)	
Units of allogenic blood transfusion transfused prior to intervention (numbers of units)	
Bleeding duration (from start of bleeding to intervention) (min.)	
Time from birth to intervention (min.)	
Baseline haemoglobin (measured before intervention) (mmol/L or g/dL)	
Method of anaesthesia: general versus regional anaesthesia	

Adjusted analysis will be provided and results may guide further research in this field.

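### The comparison named and sized for is a crude two-by-two test, and the article does not say whether it or the promised adjusted analysis decides the primary outcome; a short fixed covariate set would probably gain some power at almost no cost

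*Protocol article*

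**What the plan says.** Under Statistical methods and data analysis, the protocol article states the group comparison as follows: "The two groups will be compared using chi-square test (binominal data) or Fischer’s exact test", with the exact test for small expected counts. The same section adds that "we will present adjusted and unadjusted analyses of the possible effect", and that "The baseline variables/parameters will be assessed using multiple logistic regression models".

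The variables are those of Table 1, whose title describes them as variables "to be assessed for baseline imbalance between treatment groups in the final analysis". The table has sixteen entries, among them estimated blood loss before the infusion, mode of delivery and "Baseline haemoglobin (measured before intervention) (mmol/L or g/dL". It closes with: "Adjusted analysis will be provided and results may guide further research in this field". The text introduces the variables as possible confounders. No sentence names a final covariate set or says which of the two results, adjusted or unadjusted, answers the primary question.

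Under Outcomes and safety measures, the primary outcome is binary (transfused or not). The secondary outcomes include "the development of re-bleeding and Hb < 5.8 g/dL (3.6 mmol/L".

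**The concern.** The decision to transfuse plausibly depends largely on haemoglobin and on how much the woman has bled. Both are recorded before the study drug is given (legend of Figure 1; Haemostatic monitoring; Table 1). Under Inclusion criteria, women enter with more than 500 ml lost and a planned removal of the placenta, or with more than 1000 ml lost in the other two situations, so prognosis should vary widely between them. For the haemoglobin threshold outcome, baseline haemoglobin is the starting value of the outcome itself.

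Two things are at stake. First, a crude comparison leaves in the noise whatever variation these measurements could explain, in a trial sized at 80% power. Second, if the crude and adjusted results disagree, the article gives no rule for which one is the trial's answer.

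**Working it through.** **Inputs.** Number of participants gives alpha 0.05 (sidedness not stated; taken as two-sided), power 80%, a 33% relative reduction and 107 per group. The control risk is not stated. The same section says that about 1% of parturients are transfused and 1.75% have a blood loss above 1000 ml, which implies 1/1.75 = 57.1%. The prognostic strength of haemoglobin and blood loss is not given anywhere and is assumed over a range below.

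**Step 1: reproduce the plan's figure.** The unadjusted two-proportion formula with pooled variance is

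n = [1.96·√(2p̄(1−p̄)) + 0.842·√(p1(1−p1) + p2(1−p2))]² / (p1−p2)²

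With p1 = 0.5714, p2 = 0.5714 × 2/3 = 0.3810 and p̄ = 0.4762, this is (1.384 + 0.584)² / 0.1905², or 107 per group, with power 80.1%. With a risk ratio of 0.67 the formula gives 109, and power at 107 is 79.3%. At this control risk, a continuity correction (117 to 120) or a one-sided test (84 to 86) does not give 107. The stated size is therefore that of the crude test.

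**Step 2: approximate gain.** If the covariates explain a share R² of the outcome variance, the adjusted analysis needs about 107 × (1−R²) women per group to match the crude test with 107. Equivalently, its power is that of 107/(1−R²) per group. From a crude 79.3% (risk ratio 0.67):

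| R² | Equivalent n per group | Approximate power |
|---|---|---|
| 0.04 | 103 | 81% |
| 0.10 | 96 | 83% |
| 0.19 | 87 | 87% |
| 0.25 | 80 | 90% |

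**Step 3: simulation at about 57% control risk.** There were 107 per group and 3000 runs per row (Monte Carlo standard error about 0.7 points at 80% power). Set A uses one prognostic index and a likelihood-ratio test. Set B uses two covariates and a Wald test.

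| Set | AUC | Crude power | Adjusted power | Gain (points) |
|---|---|---|---|---|
| B | 0.50 (no prognostic value) | 80% | 80% | 0 |
| B | 0.61 | 79.4% | 81.5% | 2.1 |
| A | 0.64 | 79.5% | 82.7% | 3.2 |
| B | 0.68 | 79.2% | 83.6% | 4.4 |
| A | 0.69 | 79.1% | 83.7% | 4.6 |
| A | 0.74 | 78.4% | 85.9% | 7.5 |
| B | 0.76 | 79.2% | 87.6% | 8.4 |
| B | 0.80 | 76.9% | 89.8% | 12.8 |
| A | 0.81 | 78.4% | 90.1% | 11.7 |

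The simulated crude power at AUC 0.80 (76.9%) lies below the analytic 79.3%. Measured against the analytic value, the gain in that row is 89.8 − 79.3 = 10.5 points.

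**Step 4: dependence on the control risk.** For set B at odds ratios per standard deviation of 2, 3 and 4:

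| Control risk | Gain at 2 | Gain at 3 | Gain at 4 |
|---|---|---|---|
| 40% | 3.9 (53.8 to 57.7%) | 6.5 (53.7 to 60.2%) | 10.7 (55.7 to 66.4%) |
| 20% | 0.8 (24.8 to 25.6%) | 1.9 (26.7 to 28.6%) | 3.8 (25.1 to 28.9%) |

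**Step 5: type I error at about 57%.** In set B, with prognostic covariates, the adjusted test rejected in 3.9 to 4.9% of null runs, nearly the same as the crude test (3.9 to 4.9%). In set A it rejected in 4.9 to 5.8%.

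**Step 6: length of the list.** Expected events at the planning assumptions are 107 × (0.571 + 0.383) = 102. Spread over sixteen entries that is about 6 events per entry, before counting categories such as cause of bleeding. A short set is the practical choice for a deciding analysis.

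**The case against.** The crude test is a valid comparison for a randomised binary outcome and matches the sample size calculation. A separate analysis plan, not shown here, may name the covariates, their coding and the handling of missing values, and an article need not.

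Three stronger readings are tempting and are not supported:

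- A reader might infer that the plan ignores baseline haemoglobin and blood loss. It does not: it promises an adjusted analysis, and both are in Table 1.
- A reader might infer that the adjusted result serves future research alone. The closing line of Table 1 says that it may do so; it does not restrict it to that use.
- A reader might infer that the trial is underpowered because of the crude test. Under its own assumptions it has its planned 80%. The Discussion calls the trial a pilot when setting it against much larger trials, and that is no admission about the transfusion comparison.

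It is also fair that the article never labels the chi-square test primary. That status is inferred from its position and from the sizing.

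The size of the gain is open to challenge. The simulations assume a linear effect on the log-odds and covariates measured without error. Here blood loss is estimated and cut off below by the entry thresholds, and fluids or blood given before the infusion may blur baseline haemoglobin. The 5.8% null rejection in the strongest setting of set A is about two Monte Carlo standard errors above 5% (standard error √(0.05 × 0.95/3000) = 0.4 points), so a little of that setting's gain may be test inflation.

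What remains is that the article itself commits to the crude comparison, ties adjustment to a long imbalance list, and gives no order between the two results. Leaving detail to an analysis plan does not remove that.

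**Conclusion.** The point holds as one of efficiency and of an undecided primary result. The crude test is not an error. At the implied 57% control risk the forgone power runs from 0 points (covariates without prognostic value) through 2 to 5 (AUC 0.61 to 0.69) and 7 to 9 (AUC 0.74 to 0.76) to 12 to 13 (AUC 0.80 to 0.81). It shrinks to about 1 to 4 points at a control risk of 20%. These figures rest on an assumed prognostic strength, on a control risk that the article implies but does not state, and on a two-sided test. The absence of a rule for choosing between the adjusted and unadjusted results rests on the text alone and needs no assumption.

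**What to change.** Before unblinding, state in the analysis plan that the primary analysis of transfusion is a logistic model with treatment and a short fixed set of covariates measured before the infusion: baseline haemoglobin and estimated blood loss, both continuous, and mode of delivery. Report the standardised (marginal) risk ratio and risk difference from that model, because its odds ratio is conditional on the covariates and does not correspond to the 33% risk reduction used for sizing. Keep the chi-square or exact test as the supporting unadjusted result, and let the wider Table 1 list serve exploratory analyses.

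For the outcome of haemoglobin below 5.8 g/dL, no event rate is given. Adjust for baseline haemoglobin only if there are enough events for a stable model, and otherwise keep the exact test.

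The cost is a paragraph of text and a few lines of code, with no new data and no new participants. The small downsides are the standardisation step and the need for a simple rule for missing baseline values, such as imputing the overall mean, so that no woman is lost from the primary analysis.
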